#### Problem behavior

To assess resistance to care via external assessment, a single item and visual analogue scale, based on Wilz and Soellner [29], will be used. In addition, agitated behavior will be assessed using the German version of the Cohen-Mansfield Agitation Inventory (CMAI; [31, 32]) which measures physically aggressive behaviors (PAB; e.g. hitting), physically non-aggressive behaviors (PNAB; e.g. general restlessness), and verbally agitated behaviors (VAB; e.g. repetitious sentences or questions) over the preceding two weeks. Each of the 29 items is rated on a seven-point scale of frequency. In addition, a five-point scale (from 1 = never to 5 = extremely) will be used for measuring disruptiveness of behavior. Cronbach’s *α* for the German version is .80 [32]. Furthermore, the German version of the Nurses Observation Scale for Geriatric Patients (NOSGER; [33]) will be used. It consists of six dimensions (memory, instrumental activities of daily living (IADL), basic activities of daily living (ADL), mood, social behavior, and disturbing behavior) with five items each. Each item is rated on a five-point scale of frequency of occurrence. The test-retest reliability for the six dimensions lies between .75 and .93.

In addition, goal attainment scaling (GAS; [34]) will be used to evaluate participants’ personal goal attainment. At T1 a member of the nursing staff will specify the participant’s personal goals for the individualized music intervention (IG) or for the standard offer of activities in the nursing home regarding the following six weeks (CG) in assistance by a member of the project team. At T2 nursing staff will rate participants’ personal goal attainment on a five-point scale, where point zero denotes the initial state being maintained or remaining stable. A lower value indicates a mild (− 1) or severe (− 2) deterioration from the certain goal, whereas positive scale values represent a positive change from the initial state in the sense of partial (+ 1) or complete (+ 2) goal attainment (cf. Chew et al. [35]).

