Average personal goal attainment according to the GAS-ratings of the nursing staff will be calculated by first calculating the average personal goal attainment for each participant across all of his/her specified goals, and then calculating the average goal attainment across all participants separately for IG and CG. In addition, the proportion of participants who completely or partially attained their goals, experienced at best no change with regard to their personal goals, and the proportion who reported mild or severe deterioration on the specified goals separately for IG and CG will also be calculated. Frequency scores will be compared between the two groups.

For analyzing the behavioral observation data, frequency scores will be computed for time units 1–5 (i.e. the first 20 min of behavior observation; pre-intervention period in the IG), 6–10 (i.e. the second 20-min period; intervention period in the IG) and 11–15 (i.e. the third 20-min period; post-intervention period in the IG) by summing up how often each behavior occurred in each of the three observation periods. Frequency scores for each period will subsequently be compared both within and between intervention groups in order to identify significant changes in frequencies of behaviors.

Frequencies and percentages in each response category will be computed for the secondary outcome measures as indicators of the acceptance and applicability of the intervention.

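### Goal attainment is compared between groups only through three classes that overlap and have no rule for several goals, while no comparison is named for the average score per resident

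*Protocol article*

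**What the plan says.** Under Primary outcome measures (Problem behavior), nursing staff rate "personal goal attainment on a five-point scale, where point zero denotes the initial state being maintained or remaining stable". Below zero the scale runs to deterioration: "A lower value indicates a mild" (−1) or severe (−2) worsening. Above zero, +1 is partial and +2 complete attainment. At T1 a staff member "will specify the participant’s personal goals for the individualized music intervention (IG") or, for controls, for the home's usual activities. The plural allows several goals per resident, and the number is not fixed.

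Under Data analysis, the plan starts by "first calculating the average personal goal attainment for each participant across all of his/her specified goals" and goes on to "calculating the average goal attainment across all participants separately for IG and CG". It then adds "the proportion of participants who completely or partially attained their goals", followed by those who "experienced at best no change with regard to their personal goals, and the proportion who reported mild or severe deterioration on the specified goals". The paragraph on goal attainment closes with: "Frequency scores will be compared between the two groups".

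The same section assigns the primary outcomes to multilevel models whose first level is the four assessments, T0 to T3.

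**The concern.** Three features of the goal attainment paragraph work against each other.

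- A class meaning no better than unchanged covers every score of 0 or below, so it includes everyone who deteriorated.
- The classes suit a single rating, but residents may have several goals and nothing says how mixed ratings are combined.
- The one summary that handles several goals, the average per resident, is tabulated by group without a named comparison.

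The multilevel model cannot fill the gap. It needs values at T0, T1, T2 and T3, and goal attainment has one rating, at T2.

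At stake are reported proportions that depend on a classification rule still to be chosen, in a trial whose Discussion says blinding is not possible, and a less sensitive comparison for an outcome placed under the primary heading.

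**Working it through.** The plan gives no power or expected rate for goal attainment, so there is no stated figure to reproduce.

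**Step 1: the classes with one goal.** The scale has five points. *Attained* is {+1, +2}. *At best no change*, read literally, is {0, −1, −2}. *Deteriorated* is {−1, −2}. Two of the five ratings fall in two classes. If exactly 0 was meant, this overlap disappears, but the text does not say so.

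**Step 2: the classes with k goals.** There are 5^k rating patterns. These are counts of patterns, not of residents, and need no outside assumption.

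- *Any-goal rule, both attained and deteriorated:* 5^k − 3^k − 3^k + 1. For k = 2: 25 − 9 − 9 + 1 = 8 of 25. For k = 3: 125 − 27 − 27 + 1 = 72 of 125.
- *No goal above 0 and at least one below (both at best no change and deteriorated):* 3^k − 1, which is 8 of 25 and 26 of 125.
- *All-goals rule, in no class (some goals above 0, some not):* 5^k − 2^k − 3^k. For k = 2: 25 − 4 − 9 = 12 of 25. For k = 3: 125 − 8 − 27 = 90 of 125.
- *Average rule:* the sign of the average places every pattern on one side of 0 or at 0, but 12 of 25 and 84 of 125 patterns give a non-integer average, such as +0.5, that is not a point of the scale.

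**Step 3: how many residents this could be.** Assume each goal has a 40% chance of attainment and 25% of deterioration (neither is in the documents). With three independent goals, the share in both outer classes under the any-goal rule is 1 − 0.6³ − 0.75³ + 0.35³ = 1 − 0.216 − 0.422 + 0.043 = 0.405. With a correlation of 0.4 between a resident's goals it is about 22% for three goals, 10% for two and 0% for one. The plausible range is therefore wide.

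**Step 4: false-positive rate.** Assume true exclusive classes of 40/35/25% and 47 per arm (130 × 0.73 = 94.9 residents left after the plan's 27% dropout, halved). Under the null at a nominal 5%, simulation gives:

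- one chi-square on the overlapping 2×3 table: about 3.4%, so conservative;
- each of the three proportions compared separately: 4.6%, 4.6% and 5.1%.

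**Step 5: power.** The plan's f = 0.2 corresponds to d = 2 × 0.2 = 0.4, although it is stated for quality of life and problem behavior and not for goal attainment. Further assumptions are a normal latent score, goal correlation 0.4, scale cut-points at −1.5, −0.6, 0.4 and 1.3, 47 per arm and a two-sided 0.05. Simulated power:

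| Goals per resident | Average score, t-test | Three exclusive classes, chi-square | Same classes, rank test |
|---|---|---|---|
| 1 | 45% | 31% | 39% |
| 2 | 60% | 40% | 50% |
| 3 | 67% | 42% | 51% |

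As a plausibility check, a t-test on an uncategorised score at d = 0.4 with 46 per arm has power 0.475, so 45% for a single five-point rating is in line. Averaging raises power because the SD of the mean is √(0.4 + 0.6/k). For k = 3 this is √0.6 = 0.775, an effective d of 0.4/0.775 = 0.52.

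**The case against.** The strongest reply is that the article names no chi-square and no 2×3 table. It lists separate proportions, and nested proportions may be compared one at a time without harm. Step 4 confirms this. A reader might infer from the overlap that the test has a wrong error rate, or that percentages summing to more than 100% are a fault in themselves. The documents do not support that: the error rate departs from 5% only for a pooled table the plan does not specify, and then in the conservative direction.

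A reader might likewise take 40% as the share of residents counted as both attained and deteriorated. That figure needs three goals, independence and an any-goal rule, none of which the plan states.

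It can also be said that the average comes first in the paragraph and the proportions are additional, that classifying by the average is a natural reading, and that a test for the averages may be left to an analysis plan. This stands in part. The article says compared, not tested, and does not rule out comparing the averages. But it does attach its one comparison to the frequencies, and it does print class definitions that overlap. Those are statements in the text, not detail left out.

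Finally, a rank test on the classes recovers part of the lost power, and goal attainment is one of many measures under the primary heading. The sample size is not said to rest on it.

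**Conclusion.** The point holds as a defect of definition and a weak choice of comparison. The overlap of the two lower classes and the absence of a rule for several goals follow from the printed text alone. So does the absence of a named comparison for the average, which the multilevel model cannot supply.

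The cost in power is illustrative. Against a three-class chi-square it is about 14 points with one goal (45 − 31), 20 with two (60 − 40) and 25 with three (67 − 42). Against a rank test on the classes it is 6, 10 and 16 points. These sizes depend on the assumed shift, correlation and cut-points.

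No inflated false-positive rate is shown. This is a worthwhile, cheap improvement and not a threat to the trial's validity.

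**What to change.** Name one between-group comparison for goal attainment: a linear model of each resident's average T2 score on group, adjusted for nursing home and gender (randomization uses a list per home, stratified by gender), reported as an estimate with a confidence interval.

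For description only, place each resident once by that average (above 0, equal to 0, below 0), report these exclusive percentages by group, and attach no further test.

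The change rewords one paragraph and needs no new data. Its small downside is that an averaged ordinal score is treated as continuous.

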During the intervention period, observation of behavior will be conducted three times for 60 min for each participant using an adapted rating scale (based on the Observed Emotion Rating Scale [36] and suggestions from the music&memory working group) with 37 items. The scale is divided into 15 time units of four minutes each. In each time unit it is coded whether the behavior occurs. The aim is to identify emotional and motor changes (facial expression, body movement, and other positive emotional reactions) and activation regarding social participation as well as the occurrence of problem behaviors or other negative reactions.

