### Intervention

Participants of the IG will listen to their individualized playlists on MP3 Players and headphones for 20 min every other day over the course of six weeks for a total of 21 music sessions. During the music intervention period, the project staff or nursing home staff will accompany and monitor the participants. As no comparable control intervention is available, the CG will receive standard care. Participants of both groups can use all simultaneous offers in the nursing home. If additional music therapy activities take place, they will be systematically documented. During the six weeks of intervention, observation of behavior will be conducted for the IG and the CG every other week for 60 min (three observations per participant). In the IG, participants’ behavior will be observed for 20 min before the music listening session starts, during the 20-min listening session, and for 20 min after the end of the music listening session.

For all music listening sessions, date, time, and duration of the session as well as, if necessary, the reason why a session had to be cancelled will be recorded by project staff or staff from the nursing home using a standardized documentation sheet. The suitability of the playlists will be checked and documented during the music listening sessions and playlists will be continuously adapted over the intervention period as needed.

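### The behaviour observations are to be searched item by item, within and between arms, with no named between-arm contrast for the music effect and no key outcome or error control

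*Protocol article*

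**What the plan says.** All references are to the protocol article.

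- **Instrument** (Problem behavior, under Primary outcome measures). The scale, adapted partly from "suggestions from the music&memory working group) with 37 items", is laid out in time: "The scale is divided into 15 time units of four minutes each". Each unit is coded for whether the behaviour occurs.
- **Schedule** (Intervention). In both arms, "observation of behavior will be conducted for the IG and the CG every other week for 60 min (three observations per participant"). In the intervention group (IG), "participants’ behavior will be observed for 20 min before the music listening session starts, during the 20-min listening session, and for 20 min after".
- **Scoring** (Data analysis). Scores are formed for units 1–5, 6–10 and 11–15 "by summing up how often each behavior occurred in each of the three observation periods".
- **Comparison** (Data analysis). "Frequency scores for each period will subsequently be compared both within and between intervention groups"; the stated purpose is to find behaviours whose frequency changes significantly.

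The hypothesis served is at the end of the Background: short-term emotional, motor and communicative benefits during and after listening.

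For the questionnaire outcomes the same Data analysis section names a multilevel model, its levels, its contrasts and the group predictor. That model runs over T0 to T3, so it does not cover the three periods inside an observation.

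**The concern.** The design can isolate the short-term effect of music: both randomised arms are observed through the same three periods. The analysis sentence does not say which comparison carries that question. It puts within-arm and between-arm comparisons on the same footing, for every behaviour and period, with the stated aim of finding significant changes.

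Two things are at stake:

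- **Within-arm change.** A shift from the first to the second 20 minutes in the IG can come from time of day, staff presence or being watched. Only the control group (CG) can remove these.
- **Item-level searching.** With 37 behaviours, some will reach significance by chance. With no key behaviour or contrast fixed, nothing separates those from a real effect.

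The observations matter to the trial. They sit under the primary outcomes, and the Discussion sets them against its admitted reliance on nursing-staff ratings.

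**Working it through.** The article gives no figure for this analysis, so there is none to reproduce.

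**Inputs from the article**
- 37 items, 3 periods, 2 arms (Problem behavior; Data analysis; Design).
- 92 participants needed, allocated 1:1 (Sample size; Design): 92 / 2 = 46 per arm.
- α = .05 (Sample size).

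**Assumptions**
- .05 two-sided for each observation test.
- Approximately normal scores, one score per participant and period.
- Correlation 0.5 between periods unless stated. The SD of change is then √(2(1 − 0.5)) = 1 score SD.

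**1. Number of tests and expected chance findings (global null)**

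Expected false positives = tests × .05. The chance of at least one, if tests are independent, is 1 − .95^tests.

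| Comparisons run | Tests | Expected false positives | At least one (independent) |
|---|---|---|---|
| One between-arm test per item | 37 | 1.85 | 85% |
| Between arms in all three periods | 37 × 3 = 111 | 5.55 | 99.7% |
| Plus three pairwise period tests in each arm | 111 + 37 × 3 × 2 = 333 | 16.65 | over 99.9% |

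Items will be correlated. For 37 tests, simulation puts the chance of at least one at 72%, 55% and 36% for correlations between tests of 0.3, 0.5 and 0.7. The expected number does not depend on correlation.

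**2. Reading within-arm significance as an effect**

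Suppose both arms change equally, so music adds nothing. If each paired test has power p, the chance of significance in the IG and not in the CG is p(1 − p). With 46 per arm the noncentrality is δ√46 = 6.78δ, where δ is the change in SDs.

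- δ = 0.2: p = .262; .262 × .738 = .19
- δ = 0.3: p = .512; .512 × .488 = .25
- δ = 0.4: p = .757; .757 × .243 = .18
- No change: about .05

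Simulation of the same settings (10,000 trials each):

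| Equal change in both arms | IG significant, CG not | Between-arm test, units 6–10 | Between-arm test of change |
|---|---|---|---|
| 0 | .047 | .052 | .050 |
| 0.2 SD | .194 | .049 | .052 |
| 0.3 SD | .247 | .056 | .051 |
| 0.4 SD | .184 | .054 | .050 |

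Both between-arm tests hold their level. The within-arm reading does not.

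**3. Which between-arm test is stronger**

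For a true effect of 0.4 SD, the units 6–10 comparison has power .47 to .48. The comparison of change has power .36, .48 and .69 at correlations 0.3, 0.5 and 0.7. This follows from the variance of change, 2(1 − ρ), against 1 for a single period: the change contrast gains only when ρ exceeds 0.5.

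**The case against.** The strongest reply is that the plan already contains a sound test. Comparing IG with CG in units 6–10 compares randomised groups while only one hears music. **This stands.** A reader might infer that the planned comparisons cannot test the music effect at all; the article does not support that. Nor is change from the before period the only valid measure. That period falls inside the six intervention weeks, so subtracting it may remove carry-over or anticipation, and it does not always add power.

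A second reply is that one summary sentence is being over-read. Within and between could describe a mixed analysis, and nothing says that an effect will be claimed when only the IG is significant. **This stands too.** The 18 to 25% shows what that reading would cost; it is not a rule the article states. The article also gives no reason to expect a change of 0.2 to 0.4 SD in the CG.

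A third reply is that model family, multiplicity correction and the handling of repeated sessions may sit in an analysis plan not shown. **This stands in part.** Those omissions alone would be no finding. But the article does fix the unit (each behaviour), the comparisons (within and between) and the aim (significant changes), and that stated rule is what needs changing.

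It would also be tempting to say that the three sessions are treated as independent, or that scores run from 0 to 5. The article does not say how sessions are combined. Summed over sessions, scores would run from 0 to 15 and clustering by session would not arise.

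**Conclusion.** The point holds in a limited form. The article plans significance comparisons of 37 single behaviours over three periods, within and between arms. It does not say which between-arm contrast tests the short-term music effect, and it names no key outcome or error control. The within-arm comparisons are not evidence of a music effect; the between-arm comparison in units 6–10 is.

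The size is a range. The 333 tests behind the figure of 17 false positives are the top of an assumed count; the most favourable count still gives about 2. The false-positive counts assume that no null is violated anywhere, whereas the 18 to 25% assumes a real and equal change in both arms. They describe different situations and should not be combined.

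The change should be made before analysis. It does not put the design or the data in doubt.

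**What to change.** In Data analysis, replace the item-level within- and between-group comparisons with one between-arm analysis per domain.

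- **Domains.** Use those the article already names: emotional, motor, social participation, and problem or negative behaviours. Fix the item-to-domain mapping before analysis, since the article does not give it.
- **Model.** Fit a mixed model with group × period and random effects for participant and session. Allow for overdispersion of the bounded counts, because neighbouring four-minute units are probably correlated.
- **Key contrast.** Name it in advance: the group difference during music (units 6–10), either relative to or adjusted for the before period, and likewise for the after period. State that the before period lies within the intervention weeks and is not a pre-treatment baseline.
- **Error control.** Apply Holm over domains. With four domains the smallest p-value is judged against .05 / 4 = .0125; Bonferroni over 37 items would require .05 / 37 = .00135.
- **Reporting.** Show single items and within-arm changes descriptively only.

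No new data are needed. The cost is rewording, some modelling work and fewer claims about single behaviours.

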### Dissemination

All results of the study will be published in international and open-access journals. In addition, the results will be presented at meetings (e.g. in the participating nursing homes) and congresses.

## Discussion

This study will evaluate whether an individualized music intervention can be successfully implemented in the institutional care setting and improve the quality of life of PwD living in a nursing home.

The study has several strengths. To address the methodological limitations of previous studies, a RCT with a large sample of PwD living in multiple nursing homes is conducted. Our study also includes the systematic identification of personally-relevant music for each participant, the continuous examination and adaptation of playlists, and a higher dosage of individualized music listening sessions in comparison with the interventions evaluated in previous studies. We also address limitations of previous studies by following a careful implementation procedure and by evaluating the implementation success.

Another strength of this study is its robust design with four assessment points including a baseline, pretest, posttest, and follow-up assessment allowing the evaluation of different change patterns between IG and CG, as well as its long-term effects of the individualized music intervention. The study design also allows for controlling the progression of dementia. Additionally, the multiple, detailed and controlled observation of behavior constitutes an innovative novelty in the context of individualized music interventions. PwD with all severity stages will be included in the study.

However, there are also limitations identified in this study. First, nearly all outcomes will depend on the external assessment by the nursing staff. Nevertheless, the outcomes will be disease specific and, in our opinion, assessments by nursing staff will be most valid for this purpose. In addition, observation of behavior will be performed due to trained raters. Future research may also include physiological outcomes (e.g. cortisol, heart rate) as potential outcome measures.

Second, blinding is not possible in the design of the proposed study since the nursing home staff and project staff will accompany and monitor the participants during the intervention period and will, therefore, know which participants receive the music intervention and which do not.

On the whole, individualized music represents a promising non-invasive and low-risk intervention that can be delivered easily without a professional in contrast to active forms of music therapy (i.e. singing or moving to music). Thus, the individualized music intervention may be well integrated in the care setting and our results regarding the acceptability as well as the implementation will provide insights into this.

In summary, this will be the first study to carefully test the implementation, efficacy, and acceptability of an individualized music intervention for PwD in multiple nursing homes in Germany within a RCT including a large sample. If the individualized music intervention proves to be effective in improving primary outcomes, our results will be relevant to practice. Hence, individualized music interventions could be used as an innovative and inexpensive alternative to pharmacological interventions for PwD in the institutional care setting. Therefore, the results of the study will be used to improve the quality of life of PwD living in a nursing home.

